### Data analysis

Initially, a descriptive analysis of the data will be performed to characterize the research participants, in the form of values ​​of absolute frequency and percentage (relative) for categorical variables and values of mean and standard deviation for numerical variables.

Statistical analysis of comparison and correlation of the obtained data will be performed. The Kolmogorov-Smirnov test will be performed to analyze the sample’s normality. Depending on the results obtained in the normality test, the Analysis of Variance (data with normal distribution) or Wilcoxon and Mann-Whitney Test (non-parametric data) will be used for comparative analyzes between the groups. Likewise, Pearson or Spearman tests will be used for correlational analyzes. Categorical variables will be analyzed using the chi-square test or Fisher’s exact test. Statistical analyzes will be performed using the statistical program SAS System for Windows (Statistical Analysis System), version 9.4, adopting a significance level of 5% (p <0.05). Study endpoints will be analyzed primarily for the per protocol population, and repeated, for sensitivity reasons, for intention-to-treat population [54].

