### Sample size

The sample calculation was based on the study by Krychman *et al*. [32], who demonstrated that RF therapy was associated with significant clinical and statistically significant improvement in sexual function in women with VL, when data analysis was performed in a group containing 73 patients. To calculate the sample of the present study, we used values of sexual function assessed using the FSFI questionnaire. There was an increase of 7 points in the FSFI score in the group treated with radiofrequency and an increase of 3 points in the control group. When considering a study power of 80%, an alpha of 0.05 with two-tailed test, it was found that the minimum number of participants required in each group will be added to a percentage of 30% loss in the sample, totaling 68 women, 34 in each group (isolated RF and isolated PFMT).

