### Allocation

The randomization sequence will be carried out through a computer program, in a 1:1 allocation ratio, in two blocks. The numbers corresponding to the study groups (1. Radiofrequency and 2. Pelvic Floor Muscle Training) will be placed in opaque sealed envelopes that will be opened by the study participants after signing the consent form and undergoing initial assessment in the first clinical visit.

The researchers who will assist in completing the questionnaires and physical examination, the researchers responsible for ultrasound and the data analysts will be blinded for the treatment group to which the participants were randomized to.

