### Follow-up period assessment

Patients will be followed up in two periods after the interventions: first follow-up (30 days after intervention) and second follow-up (six months after intervention). The assessment procedures in the follow-up period will be the same as those used in the baseline physical examination, questionnaires, and ultrasound exams. We will add the Global Response Assessment.

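### Secondary outcomes are measured at baseline, but the group comparison uses no baseline covariate and lets a normality test choose the method

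*Protocol article*

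**What the plan says.** Under Baseline assessment, the protocol article collects the self-completed questionnaires, the pelvic floor strength grade, the prolapse quantification and the ultrasound measures at the first visit. Under Follow-up period assessment it repeats them at 30 days and six months: "The assessment procedures in the follow-up period will be the same as those used in the baseline physical examination, questionnaires, and ultrasound exams". The GRA is added only at follow-up.

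Under Data analysis, a Kolmogorov-Smirnov test of the sample's normality comes first. Depending on its result, "the Analysis of Variance (data with normal distribution) or Wilcoxon and Mann-Whitney Test (non-parametric data) will be used for comparative analyzes between the groups". No baseline covariate, ANCOVA or other adjusted model is named. The section does not state whether the analysed variable is the follow-up score, the change from baseline or a repeated measure.

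Under Sample size, the trial is sized on a secondary outcome, the Female Sexual Function Index (FSFI): "we used values of sexual function assessed using the FSFI questionnaire". The planning effect is framed as increases, with the 3 points belonging to the comparison arm: "There was an increase of 7 points in the FSFI score in the group treated with radiofrequency and an increase of 3 points in the".

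**The concern.** There are two linked weaknesses, and both are in choices that the article makes, not in matters it leaves open.

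First, the baseline value of each scale is collected but is not used as a covariate. A comparison of follow-up scores leaves in the error all the variance that baseline would explain. A comparison of changes uses baseline, but with a fixed coefficient of one in place of the best-fitting one, and so is also less precise than ANCOVA. In a trial of 68 women that allows for 30% loss, this matters for the precision of the secondary comparisons.

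Second, the data choose the test. The normality test is applied to the sample, not to model residuals, and may go different ways for different outcomes or, if visits are tested separately, for two visits of the same scale. When it selects the rank test, the result is not a mean difference in FSFI points, so it cannot be set beside the planning difference. The rank test also takes no covariate.

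**Working it through.** **Inputs from the protocol article.** Two-sided alpha 0.05 ("an alpha of 0.05 with two-tailed test"), power 80%, an FSFI difference of 7 − 3 = 4 points, 30% loss and 34 women per arm ("will be added to a percentage of 30% loss in the sample, totaling 68 women, 34 in each group"), and equal allocation ("in a 1:1 allocation ratio, in two blocks").

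**Inputs not given.** The FSFI standard deviation (SD) and the baseline-to-follow-up correlation r. Both are assumptions below, and r is shown from 0.3 to 0.7.

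**The plan's own figure.** The total of 68 cannot be reproduced without an SD, but the implied SD can be back-solved. With n per arm = 2·SD²·(1.960 + 0.842)²/4², we have SD = 4·√(n/2)/2.802.
- If 34 is the number before 30% loss, 34 × 0.7 = 23.8, about 24 evaluable, and SD = 4.95.
- If 34 is the evaluable number times 1.3, 34/1.3 is about 26 evaluable, and SD = 5.15.

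An SD of 4.9 is used below; it gives 24 per arm.

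**Variance of ANCOVA relative to the stated methods** (large-sample, with equal variance at baseline and follow-up for the change-score case):
- against follow-up scores: 1 − r²
- against change scores: (1 − r²)/(2(1 − r)) = (1 + r)/2

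Both ratios are below 1 for any r strictly between 0 and 1, so the direction does not depend on the assumed value. The extra women needed by the unadjusted method follow from the reciprocals.

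| r | Follow-up score, 1/(1 − r²) | Change score, 2/(1 + r) |
|---|---|---|
| 0.3 | 1.099 (+10%) | 1.538 (+54%) |
| 0.4 | 1.190 (+19%) | 1.429 (+43%) |
| 0.5 | 1.333 (+33%) | 1.333 (+33%) |
| 0.6 | 1.562 (+56%) | 1.250 (+25%) |
| 0.7 | 1.961 (+96%) | 1.176 (+18%) |

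**Repeated-measures reading.** With baseline and one follow-up, the group-by-time test is the change-score test, so the last column applies. With both follow-ups, the contrast of each visit against baseline is again a change-score contrast.

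**In terms of power.** If 4.9 is the SD of the follow-up score, 24 per arm gives 0.81 unadjusted. With adjustment this becomes 0.84, 0.90 and 0.98 at r = 0.3, 0.5 and 0.7. If instead a change-score test has 80% power, adjustment gives about 94%, 90% and 86% at the same values.

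**Simulation check** (normal data, 24 per arm, follow-up SD 4.9, 3,000 runs for each r):

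| r | Follow-up score | Change score | Mann-Whitney on follow-up score | ANCOVA |
|---|---|---|---|---|
| 0.3 | 0.79 | 0.65 | 0.77 | 0.81 |
| 0.5 | 0.79 | 0.79 | 0.77 | 0.88 |
| 0.7 | 0.79 | 0.94 | 0.76 | 0.97 |

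The small-sample ANCOVA figures are slightly below the formula values, but ANCOVA has the highest power in every row.

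**The case against.** The strongest reply is that the article never says the analysis ignores baseline. Analysis of variance may mean a repeated-measures version, Wilcoxon may mean the paired test, and the FSFI planning effect is expressed as increases. This stands as a point about wording: calling the analysis a plain follow-up comparison would be one reading stated as fact. It does not rescue the plan, because the change-score and group-by-time readings also lose precision to ANCOVA, and the rank branch has no covariate.

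The reply is also right that several stronger readings go beyond the text:
- A reader might infer that the plan costs a third more women. That figure needs r = 0.5, which is not in the document, and one r is unlikely to fit questionnaires, an ordinal palpation grade and ultrasound alike.
- A reader might infer complete-case analysis or a separate analysis of each visit. The Data analysis section states neither.
- A reader might infer that chance baseline imbalance passes directly into the result. That holds only if follow-up scores are compared; with changes, baseline is subtracted.
- A reader might infer that FSFI loses most because it sized the trial. No figure in the document ranks its correlation against those of the other measures.

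Finally, an unadjusted comparison of randomised groups is unbiased in expectation. The point concerns precision and pre-specification, not bias.

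**Conclusion.** The point holds for the secondary outcomes. The article commits to a group comparison with no baseline covariate, selected by a normality test, although the baseline values will be in hand. On any reading of which variable is analysed, a baseline-adjusted model is more precise for r between 0 and 1.

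The size rests on an assumed r. Over 0.3 to 0.7 the stated methods need 10% to 96% more women if follow-up scores are compared, or 54% to 18% more if changes are compared. For the ordinal Oxford grade these factors are only approximate. The weakness of choosing the method by a pre-test does not depend on r.

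A reader might take this as a threat to the trial's main result. The document does not support that: the primary GRA is rated against the time before treatment, exists only at follow-up, and has no baseline value to adjust for. The change is worth making, but the primary comparison does not depend on it.

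**What to change.** In the Data analysis section, replace the choice driven by the normality test for the continuous secondary outcomes (FSFI, the sexual distress scale, the two ICIQ scores and the ultrasound measures) with one model stated in advance. This can be ANCOVA at each visit, or a mixed model with baseline value, arm, visit and arm-by-visit. Report radiofrequency minus pelvic floor muscle training with a 95% confidence interval at 30 days and at six months, in the analysis populations that the plan defines. A woman with no follow-up value adds no outcome to such a model, so it should not be described as using every randomised woman.

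Name one robust method in advance, for example a bootstrap interval, and run it as a sensitivity analysis whatever the data look like; a fallback triggered by skewness would bring back the data-driven choice. For the Oxford strength grade, use a baseline-adjusted ordinal model.

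The cost is revised wording and slightly more analysis work. No new data or visits are needed, and the article reports that the trial is still recruiting.

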To our knowledge, to date, no clinical trial has been developed to assess the role of pelvic floor muscle and radiofrequency training in VL. Thus, the general objective will be to compare the effect of RF and PFMT in women with VL symptoms. The specific objectives are related to the assessment of the sexual function, vaginal symptoms, and sexual distress, as well as, to assess the impact of UI on patients’ quality of life. The POP staging, contractility, and pelvic floor muscle function will be also evaluated. Finally, we will assess the impression of improvement in VL complaints after the interventions.

Our hypothesis is that RF will be different from PFMT in treating women with VL symptoms.

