**Fig 1 pone.0259650.g001:**
[figure not shown]
Description of the study steps. F1: Follow-up (30 days after intervention); F2: Follow-up (6-months after intervention); w: week; PFMT: Pelvic Floor Muscle Training; BMI: Body Mass Index; ICIQ-VS: International Consultation on Incontinence Questionnaire—Vaginal Symptoms; ICIQ-SF: International Consultation on Incontinence Questionnaire Short-Form.

The term VL was recently defined and little is known about this complaint. There is still no gold standard treatment for VL and further studies are needed to understand its pathophysiology. Although its pathophysiology is not completely known, there is a consensus on the association of VL with pregnancy and childbirth [2, 10, 27]. Some proposed mechanisms involve overstretching of the vaginal walls and introitus during vaginal birth and an increase in levator ani hiatal dimensions resulting from macro and microtrauma of the levator ani muscle [7, 17]. Although supervised PFMT is recommended as a first-line treatment for stress or mixed UI in women by most of the guidelines [28–30], more studies are needed to demonstrate the effect of PFMT on female sexual function. A randomized controlled trial concluded that women reporting improvement in sexual function demonstrated greatest increase in PFM strength and endurance [31].

Regarding RF, a recent randomized, multicenter, sham-controlled clinical trial found a statistically significant and clinically important improvement of VL with RF when compared with Sham treatment [32]. In our study, RF will be applied once every 4 weeks (a total of three applications) and will probably be less likely to face problems related to treatment adherence when compared to PFMT. Although the RF procedure has been shown to be well tolerated, adverse effects may occur [32, 33]. PFMT is generally free of adverse effects.

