#### 1- Radiofrequency

The RF group will receive three radio frequency applications at 4-week intervals, (an initial application, a second application after four weeks, and a third application also after four weeks) comprising 12 weeks of intervention. The four-week period between applications will allow adequate healing of the vaginal tissues submitted to the application of radiofrequency. The procedure will be performed by a trained researcher ([name]) with a supervision of an experienced urogynecologist ([name]/[name]).

The Wavetronic 6000 Touch device with the Megapulse HF FRAXX system (Loktal Medical Electronics, São Paulo, Brazil) will be used, equipped with an electronic energy fractionation circuit, connected to a vaginal electrode with 64 microneedles 200μ in diameter and 1mm in length, and divided into an array of eight columns, with eight needles each. When pressing the trigger pedal, these 64 needles are not energized simultaneously and the energy release is randomized in columns of eight needles in a predefined sequence, which does not allow two adjacent columns to fire in sequence, preventing the thermal sum of the columns (control fractional firing system (*Smart Shoot*). This allows for cooling between the points and the preservation of tissues adjacent to the vaporized points, so that neocolagenesis and neoelastogenesis can occur, through fibroblastic stimulation [24].

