*1*.*1-Procedure*. Topical anesthesia in the posterior vestibule and vaginal opening (mucosa) with 2% lidocaine gel, 2 to 3 minutes before the procedure (Table 1). A patient in a lithotomy position, with the lower limbs flexed and supported, will be introduced a disposable (high-impact polystyrene) vaginal speculum. A careful vaginal examination will be performed for any changes in the vaginal wall. Whiff test will be performed using a swab to collect vaginal discharge. A drop of 10% potassium hydroxide will be added over the vaginal secretion [36]. If a characteristic fishy odor is felt, the patient will not undergo RF and will be referred for evaluation of possible vaginosis. If the vaginal wall is intact and the whiff test is negative, the procedure will be continued, starting with topical anesthesia of the vaginal walls with 10% lidocaine spray. After 2 minutes, vaginal antisepsis with 2% aqueous chlorhexidine and cleaning with sterile 0.9% saline will be performed. After cleaning, the entire liquid content of the serum will be wiped with sterile gauze before starting to apply the RF.

**Table 1 pone.0259650.t001:** Pelvic floor muscle training and radiofrequency sessions according to the treatment duration.

Period	Interventions			
	Radiofrequency	Pelvic Floor Muscle Training		
**1 to 4 weeks**	1^st^ application	1^st^ phase	2^nd^ phase	3^rd^ phase
	• 2% Lidocaine Gel • Vaginal Examination with speculum • Whiff Test • 10% lidocaine spray • Cleaning: 2% aqueous chlorhexidine and sterile 0.9% saline • RF: 45Watts, Low Energy program (40 milliseconds) • Post-procedure orientation: 10-day sexual abstinence	• PFM maximum contraction (6 r / sustained 6 s/ 6 s rest: 1 time). Supine position. • PFM maximal contraction + transverse contraction (6 r / sustained 6 s/ 6 s rest: 1 time). Supine position. • PFM maximal contraction + hip elevation (6 r / sustained 6 s/ 6 s rest: 1 time). Supine position.	• PFM maximum contraction (1 cough / 3 r). Supine position. • PFM maximal contraction with the lower limbs extended and abducted (6 r / sustained 6 s/ 6 s rest: 2 times). Supine position. • PFM contraction in three stages—mild, moderate, maximum (6 r: 2 times). Sitting position. • PFM maximal contraction (6 r / sustained 6 s/ 6 s rest: 2 times). Standing position.	• Pelvic mobilization (anterior and posterior tilts, lateral tilts and rotation of the pelvis). Standing position. No PFM contraction in this phase. 10 repetitions each pelvic movement.

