#### 2- Pelvic floor muscle training

The patients in the PFMT group will be assisted during the sessions by an experienced physiotherapist ([name]). The participants of this group will have 12 individual sessions of supervised PFMT, lasting 40–60 minutes, once a week, and totaling 12 weeks of treatment and continue their treatment with home PFMT program. To follow the treatment at home, patients will receive a printed diary containing the complete PFMT program, with figures illustrating the positions and orientations for each exercise for the pelvic floor muscles. Patients will have the possibility to contact the physiotherapist for questions regarding home treatment by video call, audio call or messages through a telephone number made available exclusively for the study. Patients will be instructed not to perform other exercises for the pelvic floor, different from the exercises proposed by the intervention program of the present study. Our intervention program for PFMT is based on the studies of Bo *et al*. [37] and Dumoulin *et al*. [38].

*2*.*1- Procedure*. The first PFMT session is longer and focused on the careful evaluation of the pelvic floor muscles in order to identify any muscle condition that interferes with the progress of the intervention; guidance on the correct performance of the pelvic floor muscle contraction with the aid of vaginal palpation and educational material; presentation of the PFMT program; and finally, the first sequence of exercises.

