Patients will be instructed to perform three phases of exercise in each session, with at least two sessions of the PFMT program per day (Table 1). The exercises will undergo progression every 4 weeks of intervention, totaling three progressions (6 repetitions, sustained for 6 seconds, 6 seconds for rest, 8 repetitions, sustained for 8 seconds, 8 seconds for rest, and 10 repetitions, sustained for 10 seconds, 10 seconds for rest). The first phase comprises three exercises of maximum contraction of the pelvic floor muscles in the supine position, with the lower limbs semiflected and the feet supported, associated with contraction transverse exercise, and hip elevation. The second phase comprises pre-contraction of the pelvic floor muscles associated with cough; maximum sustained contraction in the supine position with the lower limbs extended and abducted; fast contractions in both supine and sitting positions, contraction in three stages (mild, moderate, maximum) in a sitting posture; maximum sustained contraction in standing posture and four supports (hands and knees). The third phase comprises the relaxation period with breathing exercises associated with pelvic mobilization in a standing posture. No pelvic floor muscles contraction in this phase. Patients will be instructed on the importance of adhering to the PFMT. In case of two absences, the patients will be contacted and their permanence in the study will be reassessed.

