### Harms

The suspension of the intervention will occur through the verification of significant levels of discomfort during the application of vaginal RF (Visual Analogue Scale), as well as the significant occurrence of events such as urinary tract infection, vulvovaginitis, irritation and vaginal injury after application of vaginal RF (telephone contact). In these cases, an appropriate medical treatment will be offered. Women will be discontinued if they miss any radiofrequency sessions or if their presence in physiotherapy sessions does not reach 80%.

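### The primary analysis is per protocol although the hypothesis is one of difference, so the headline comparison rests on a set selected after randomisation

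*Protocol article*

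**What the plan says.** Data analysis ranks the two populations: "Study endpoints will be analyzed primarily for the per protocol population, and repeated, for sensitivity reasons, for intention-to-treat population [54"]. The Introduction gives the aim of the comparison: "Our hypothesis is that RF will be different from PFMT in treating women with VL symptoms". Sample size uses a two-tailed test at 0.05 with 80% power. The Discussion mentions that the therapies might prove equally effective, but no margin appears there or elsewhere.

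The text that bears on who stays in the set is spread over several sections:

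- Harms: "Women will be discontinued if they miss any radiofrequency sessions or if their presence in physiotherapy sessions does not reach 80" per cent. The same section provides for suspending the intervention for discomfort, infection, irritation or injury, and does so for RF only.
- Planned sessions, RF: "The RF group will receive three radio frequency applications at 4-week intervals". PFMT participants "will have 12 individual sessions of supervised PFMT".
- PFMT, 2.1-Procedure: "In case of two absences, the patients will be contacted and their permanence in the study will be reassessed".
- RF, 1.1-Procedure, on a positive whiff test: "If a characteristic fishy odor is felt, the patient will not undergo RF and will be referred for evaluation of possible vaginosis".
- Trial design, on RF: it "will probably be less likely to face problems related to treatment adherence when compared to PFMT".

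**The concern.** In a trial that looks for a difference, randomisation makes the arms comparable only while women are analysed as allocated. A per-protocol set is formed by what happens afterwards. Giving it weight is usually argued for in non-inferiority or equivalence trials, and this is neither.

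This trial is exposed for three reasons. The thresholds differ by arm. The article itself expects adherence to differ. The primary outcome, the Global Response Assessment (GRA), is a self-rating by women who open their own allocation envelope. A woman who feels no benefit may well attend less, so leaving the set could plausibly be related to outcome.

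The planned intention-to-treat repeat helps only if outcomes are collected from women who stop treatment. The wording in Harms and in 2.1-Procedure leaves that open.

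**Working it through.** The plan gives no figure on this point to reproduce, and the choice of population does not depend on the sample size of 34 per group. The check has four steps.

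**1. Thresholds (from Harms and the two intervention sections).**
- RF: 3 sessions, none may be missed (2/3 = 66.7% fails).
- PFMT: 80% of 12 = 9.6, so 10 are needed. 10/12 = 83.3% passes and 9/12 = 75% fails, so two absences are tolerated. The two-absence reassessment in 2.1-Procedure is triggered while a woman still meets 80%.

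**2. What the rules alone do.** Assume each session is missed independently with probability q.
- RF: 1 − (1 − q)³.
- PFMT under Harms: P(Binomial(12, q) ≥ 3).
- PFMT if two absences led to removal: P(Binomial(12, q) ≥ 2).

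| q | RF | PFMT, three or more absences | PFMT, two or more absences |
|---|---|---|---|
| 5% | 14% | 2% | 12% |
| 10% | 27% | 11% | 34% |
| 15% | 39% | 26% | 56% |

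Under the Harms rule RF is filtered harder at these rates. If two absences led to removal, the order reverses at 10% and 15%. If RF visits are missed less often, as the article expects, the two can cancel: 5% per RF visit and 11% per PFMT visit give 14.3% versus 13.8%.

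**3. Effect on a response rate.** Let P be the true response, f the fraction excluded and pN the response among the excluded. Response in the kept set = (P − f·pN)/(1 − f), so each arm shifts by f/(1 − f) × (P − pN). Assume P = 55% in both arms, so the true difference is zero.

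- RF 10%, PFMT 30% excluded, pN = 25%: RF (0.55 − 0.025)/0.90 = 58.3%; PFMT (0.55 − 0.075)/0.70 = 67.9%. Gap 9.5 points, favouring PFMT.
- Same exclusions, pN = 40%: 0.51/0.90 = 56.7% versus 0.43/0.70 = 61.4%. Gap 4.8 points.
- PFMT exclusion raised to 40%, pN = 25%: 0.45/0.60 = 75.0% versus 58.3%. Gap 16.7 points.
- Opposite ordering, using the 10% row of step 2 under Harms (RF 27.1%, PFMT 11.1%), pN = 25%: RF (0.55 − 0.0678)/0.729 = 66.2%; PFMT (0.55 − 0.0278)/0.889 = 58.7%. Gap about 7.4 points, now favouring RF.
- pN = 55%, or the same f and pN in both arms: gap zero.

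**4. Type I error.** A simulation with no true effect used 34 per arm, a generic continuous outcome, 20,000 runs, and the Harms thresholds at q = 5% and 10%. r is the assumed correlation between staying in and outcome. Intention-to-treat, with all outcomes known, held 0.048 to 0.051 throughout. Per protocol gave:

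| Assumed r | Type I error |
|---|---|
| 0 in both arms | 0.048–0.049 |
| 0.3 in both arms | 0.058–0.059 |
| 0.5 in both arms | 0.071–0.072 |
| 0.3 in RF only | 0.066–0.075 |
| 0.5 in RF only | 0.080–0.134 |

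**The case against.** The best defence has four parts.

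- **The set is undefined.** Harms speaks of suspending the intervention and of women being discontinued; it does not say they leave an analysis set. An article may leave that definition to a fuller document. This stands: the link between the attendance thresholds and the per-protocol set is an inference, although no other attendance thresholds are given.
- **Different thresholds are not an error.** Three monthly procedures and twelve weekly sessions can hardly share one rule, and step 4 shows no inflation when removal is unrelated to outcome. This also stands. The unequal rules can aggravate the problem; they do not create it. A per-protocol primary analysis of a difference hypothesis would be exposed under identical rules too.
- **The examples are chosen.** All response, exclusion and miss rates are assumptions, and they do not agree on which arm is filtered harder. That is so, and the direction must be left open.
- **Intention-to-treat is already planned**, and Data collection and management says participants are contacted and monitored by telephone. This makes the remedy easy, but does not change which analysis is primary or say that women who stop treatment are still assessed.

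A reader might infer more: that women harmed by RF are dropped from the efficacy comparison, or that the attendance rules remove women from the study so that intention-to-treat must lack their data. The article says neither. Suspension may be temporary, discontinuation may mean treatment only, and 2.1-Procedure promises a reassessment, not removal. The cited reference may hold a rationale for the ranking, but none is given in the text.

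**Conclusion.** The concern holds for the ranking of the populations. For a two-sided difference hypothesis without a margin, the article makes the unprotected comparison primary and the protected one a sensitivity analysis.

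The size of the bias cannot be read from the article. Under the stated assumptions it is about 5 to 10 points of response, larger if exclusion is more unequal, and zero if exclusion is unrelated to outcome or equally selective in both arms. It is tempting to say that the unequal thresholds favour a particular arm. The documents do not support that: the Harms rule, the two-absence trigger and the expected adherence pull in different directions.

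That the thresholds shape the per-protocol set, and that follow-up might stop, are reasonable inferences and no more. The second matters because the intention-to-treat analysis needs those outcomes.

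**What to change.** 1. In Data analysis, make intention-to-treat (all randomised women, as allocated) primary and per protocol the sensitivity analysis.
2. In Harms and in 2.1-Procedure, state that stopping treatment does not stop follow-up. Seek the GRA and questionnaires from every randomised woman at 30 days and six months, by telephone or online if needed.
3. Reconcile the RF procedure, 2.1-Procedure and Harms on what counts as a missed session, including one withheld after a positive whiff test, and on how the two-absence reassessment relates to the 80% rule. The clinical stopping rules need not change, and which attendance rule is right is not judged here.

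The sample size is unaffected, and both analyses are already planned. The cost is an amendment while recruitment is under way, notified by the route in Study amendments, and a few extra contacts. The effect estimate may be slightly diluted by women who did not complete treatment. Outcomes of women already discontinued may not be recoverable, which is a reason to act soon.
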